#### Endpoints

**Primary endpoint**.

Freedom from disease progression (FFDP), defined as clinical failure or biochemical failure per the Phoenix definition [20].

**Secondary endpoints**.

Progression free survival (PFS), defined as biochemical failure, clinical failure, or death from any cause.Distant metastasis free survival [21].Prostate cancer specific survival (PCSS).Longitudinal PSA response.Time to salvage treatment.Physician-reported GU/GI toxicity at 1, 3, 6, 9, 12, 18, 24-months (CTCAE).Patient-reported GU/GI toxicity at 1, 3, 6, 9, 12, 18, 24-months (IPSS, EPIC, SHIM).

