#### Analysis plan

The primary endpoint of this study is failure from disease progression (FFDP), defined as clinical or biochemical disease recurrence (biochemical failure as per PSA nadir + 2 ng/mL), excluding death. Death with no evidence of progression will be treated as a competing risk in the survival models. This study will utilize both an intent-to-treat and per-protocol analysis of the primary and secondary endpoints, with time-to event duration originating at random assignment. Prognostic characteristics, treatment delivery, and toxicity will be reported using descriptive statistics. Time-to-event endpoints will be calculated using the Kaplan-Meier method [24] and compared using the log-rank test. HRs with 95% CI will be computed using the Cox proportional hazards regression model for the end point–specific hazard. Frequency distributions of grade (0 to 5) for selected adverse events will be compared using x^2^ tests. 2 × 2 sub-tables will be formed to evaluate the differences in risk of grade 2 or 3 events, and relative risk (RR) estimates with 95% CIs will be computed. The definitive analysis is planned to occur at 5 years, with two planned interim safety analysis at mean follow up of one and two years.

Secondary endpoints (unpowered) will include progression free survival (PFS), distant metastasis-free survival (DMFS), prostate cancer-specific survival (PCSS), longitudinal PSA response, and time to salvage treatment, also assessed at five years. Both patient-reported and physician-reported treatment related adverse effects at six months, one, and two years will be compared and reported. In the setting of multiple secondary endpoints, the Benjamini-Hochberg FDR correction procedure will be applied. Treatment related AE will be primarily objectively measured using the EPIC-26 evaluation. MIDs for each of the domains will be set as follows: 5 for bowel and hormonal, 6 for urinary obstructive, 11 for sexual, and 8 for urinary incontinence [25].

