## Conclusion

SABR-Dual is a prospective randomized phase II/III study comparing standard 5-fraction SABR to a novel 2-fraction SABR regimen, appropriately powered to demonstrate non-inferiority. The 2-fraction dose is firmly rooted in a mature experience using HDR-brachytherapy. Radiation delivery on this study is accessible and widely generalizable as expensive and limited technologies such as MR-LINAC, adaptive planning, and daily rectal probe insertion are not mandated. Such treatment, if shown to be non-inferiorly safe and effective as standard 5-fraction SABR, may become a practice altering new standard of care in the treatment of low- and favorable intermediate-risk prostate cancer.

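### As written, the Benjamini-Hochberg correction takes in the toxicity comparisons, which raises the chance that a real excess of toxicity is called non-significant

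*Protocol article*

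**What the plan says.** All references are to the protocol article.

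- **Endpoints.** The secondary endpoints are five efficacy outcomes and two toxicity outcomes. The toxicity outcomes are "Physician-reported GU/GI toxicity at 1, 3, 6, 9, 12, 18, 24-months (CTCAE") and "Patient-reported GU/GI toxicity at 1, 3, 6, 9, 12, 18, 24-months (IPSS, EPIC, SHIM").
- **Analysis plan, second paragraph.** It opens with "Secondary endpoints (unpowered) will include progression free survival (PFS), distant metastasis-free survival (DMFS), prostate cancer-specific survival (PCSS"), followed by longitudinal PSA response and time to salvage treatment. Then comes "Both patient-reported and physician-reported treatment related adverse effects at six months, one, and two years will be compared and reported". The next sentence is "In the setting of multiple secondary endpoints, the Benjamini-Hochberg FDR correction procedure will be applied". The text then returns to treatment-related adverse effects and the EPIC-26 minimally important differences.
- **Analysis plan, first paragraph.** "Frequency distributions of grade (0 to 5) for selected adverse events will be compared using x^2^ tests". Relative risks with 95% confidence intervals are planned for grade 2 or 3 events.
- **Objective and Conclusion.** The Objective includes non-inferiority of quality of life. The Conclusion looks ahead to a change of practice "if shown to be non-inferiorly safe and effective as standard 5-fraction SABR".
- **Sample size.** The only margin in the article is 7 percentage points on 5-year biochemical progression-free survival. None is given for toxicity or quality of life.

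**The concern.** Benjamini-Hochberg limits the share of false positives among the differences that are declared. That suits claims of benefit. For toxicity in this trial the more harmful error is the opposite one: a real excess in the 2-fraction arm that goes unflagged. An adjusted p-value is never smaller than the raw one, so including toxicity in the family can only make that error more frequent.

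Two features of the plan add to this. First, a chi-square test of difference with no margin cannot itself establish non-inferior safety, so a non-significant result is easily taken as support for it. Second, the five efficacy endpoints in the family should show little or no difference if the regimen works as hoped. They then enlarge the family and mainly raise the hurdle for a toxicity signal.

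**Working it through.** **The plan's own figure.** The article gives no figure for the toxicity comparisons, but its sample size fixes the number per arm. With 90% in both arms, a margin of 0.07, one-sided 0.05 and 80% power:

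n = (1.645 + 0.842)² × (2 × 0.90 × 0.10) / 0.07² = 6.18 × 0.18 / 0.0049 ≈ 227.2, rounded up to 228 per arm, 456 in total.

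This matches the stated target.

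**Assumed inputs.** The article gives neither toxicity rates for this trial nor the composition of the family, so these are assumptions:

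- A toxicity rate of 10% vs 20%, two-sided tests at 0.05 and a false discovery rate of 0.05.
- Family of 7: the seven secondary endpoints, one test each.
- Family of 20: 5 efficacy endpoints + (physician GU, physician GI, IPSS, EPIC, SHIM) × 3 time points (six months, one year, two years) = 5 + 15.
- For simplicity, every harmed comparison is given the same standardised effect.

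**Unadjusted test.** Standard error = √(0.10 × 0.90/228 + 0.20 × 0.80/228) = 0.0331. Expected z = 0.10/0.0331 = 3.02. Power = Φ(3.02 − 1.96) = Φ(1.06) ≈ 0.855, so the miss rate is about 14%.

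**Corrected test, one harmed comparison.** If nothing else in the family is rejected, the harmed comparison must reach p ≤ 0.05/m.

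- m = 7: threshold 0.0071, critical z 2.69. Power Φ(0.33) ≈ 0.63, miss rate about 37%.
- m = 20: threshold 0.0025, critical z 3.02. Power Φ(0.00) ≈ 0.50, miss rate about 50%.

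The step-up rule is slightly more lenient, because a chance rejection elsewhere relaxes the threshold. Simulating the full procedure gives:

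| Scenario (10% vs 20%, 228 per arm) | Unadjusted | Benjamini-Hochberg |
|---|---|---|
| One harmed comparison, family of 7: missed | 14% | 36% |
| One harmed comparison, family of 20: missed | 14% | 49% |
| Three harmed time points, family of 20, correlation 0.5: a given one missed | 14% | 41% |
| Same: none of the three flagged | 3% | 23% |

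**Sensitivity.**

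- *More patients.* With 251 per arm (502/2) and one harmed comparison, the miss rate goes from about 11% to about 31% (family of 7) or 43% (family of 20).
- *Smaller effect.* For 10% vs 18% with 228 per arm and one harmed comparison in a family of 7, power falls from about 0.70 to 0.42.
- *Broader harm.* With 7 of 19 comparisons harmed at 10% vs 20%, power for a given comparison is about 0.70, a miss rate of about 30%. With 6 of 20 harmed, the chance that none is flagged is about 5% if the 0.5 correlation holds only within blocks of three tests, and about 12% if it holds across all tests.

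The direction follows from the procedure alone. The size depends on the assumed rates, the family and how widely the harm is spread.

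**The case against.** Four arguments can be made on the other side.

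1. **The family is not stated.** The Analysis plan names five efficacy outcomes as secondary endpoints and puts adverse effects in a separate sentence, while the chi-square and relative-risk methods appear a paragraph earlier with no mention of a correction. Defining the family is commonly left to the statistical analysis plan, and this is a condensed article. That stands as a limit: nowhere does the text say that every toxicity comparison is corrected. But the Endpoints section makes toxicity a secondary endpoint, and the correction follows directly on the adverse-effect comparisons without exempting them. The point is about a rule that is stated, not about detail that is absent.

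2. **No decision rule ties safety to a non-significant test.** A reader might infer that the 2-fraction arm would be read as equally safe after a corrected non-significant result. The article does not say so. Its phrase about being non-inferiorly safe is a conditional closing remark, toxicity is also to be summarised descriptively, and no adjustment of the confidence intervals is stated. A real excess would remain visible in the rates and intervals.

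3. **Safety oversight does not depend on the correction.** The committee reviews the first three and the first 20 patients, toxicity every year, and grade 3 to 5 cases. Two interim safety analyses are planned, and nothing applies the correction to them. This stands. It protects patients during the trial, but does not settle how the final between-arm comparison is reported, and the case review does not cover grade 2 events.

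4. **The missing margin is the deeper gap.** Even the unadjusted test misses about 14% in the main scenario, and false discovery rate control over many patient-reported outcomes is a defensible choice. Both are true. That is why the fix must also say what a safety conclusion rests on; lifting the correction alone would not be enough.

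**Conclusion.** The concern holds in a limited form. Read together, the Endpoints section and the Analysis plan place toxicity in the Benjamini-Hochberg family. Because toxicity has only difference tests and no margin, the correction works against the trial's own aim on safety and quality of life. Under the assumed rates and families, the chance of missing a single real excess rises by a factor of about 2.5 (36/14) to 3.5 (49/14).

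The documents do not support saying that every toxicity comparison is certainly corrected, or that the plan would lead to the experimental arm being declared equally safe. The planned relative risks with 95% confidence intervals and the committee review soften the consequence, but the article does not name them as the basis of the safety conclusion. This is a change that should be made because it is cheap; it does not invalidate the design.

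**What to change.** Three changes to the Analysis plan:

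1. Confine the Benjamini-Hochberg correction to the secondary efficacy endpoints: PFS, DMFS, PCSS, longitudinal PSA response and time to salvage treatment.
2. Report the physician- and patient-reported toxicity comparisons with unadjusted p-values and with unadjusted 95% confidence intervals for the risk difference and the relative risk.
3. State that any conclusion of similar or non-inferior safety rests on the upper confidence limit of the excess toxicity, and not on a non-significant test, adjusted or unadjusted.

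The cost is a few sentences, with no extra patients or data. The downside is that about 1 in 20 toxicity comparisons with no true difference will be flagged by chance and will have to be read clinically.

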#### Pretreatment evaluation

Patients will undergo prostate cancer diagnostic evaluation with at least a standard whole-gland sextant biopsy to establish Gleason score. MRI-guided targeted biopsy is allowed as well but comprehensive whole-gland biopsy is required. An updated staging PSA will be obtained within 1 month prior to enrollment.

All patients are required to undergo a diagnostic multiparametric MRI (mpMRI) with 3T coil to identify regions suggestive of high-grade disease and to radiographically rule out the likelihood of extra-prostatic extension and/or seminal vesicle (SV) involvement. As eligible patients will have a categorization of low-risk or favorable intermediate-risk disease, systemic staging with a CT, bone scan, and/or PSMA-PET is allowed but will not be mandated.

Prior to enrollment patients will undergo a general physical exam. Baseline urinary, sexual, and bowel symptoms will be quantified using the International Prostate Symptom Score (IPSS), Sexual Health in Men (SHIM) score, and the global quality of life measure EPIC-26.

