#### Patient monitoring

Baseline assessment will include PSA, quantitative urinary function (IPSS), sexual health (SHIM) score, and a global quality of life measure (EPIC-26). Follow up will occur at 1 month, 3 months, continuing at 3-month intervals through 1 year, then every 6 months from years 2–5, followed by annually thereafter. PSA will be recorded in follow up at 3, 6, 9, and 12 months in the first year, then every 6 months thereafter through five years, then annually. IPSS, SHIM and EPIC scores will be recorded during each follow up.

Adverse events (AE) will be described using the grading scales found in the revised NCI Common Terminology Criteria for Adverse Events (CTCAE), version 5.0. An AE is defined as any untoward medical occurrence associated with the use of a medical intervention, which in the context of this trial include radiopaque hydrogel spacer and fiducial marker placement, and radiation therapy. The following AEs should be assessed and recorded at each protocol mandated data collection interval: dysuria, hematuria, incontinence, urinary retention, diarrhea, rectal hemorrhage, fatigue. Full schedule of patient monitoring is summarized in Table 4.

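### The Analysis plan makes EPIC-26 the primary, objective measure of treatment-related AEs, which conflicts with CTCAE grading elsewhere, and one sentence leaves the attribution rule for the toxicity comparison unclear

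*Protocol article*

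**What the plan says.** The sentence at issue is near the end of the Analysis plan: "Treatment related AE will be primarily objectively measured using the EPIC-26 evaluation". MIDs in points for the EPIC-26 domains follow it: 5 for bowel and hormonal, 6 for urinary obstructive, 8 for urinary incontinence and 11 for sexual.

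Other sections describe the two instruments differently:

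- Patient monitoring: "Adverse events (AE) will be described using the grading scales found in the revised NCI Common Terminology Criteria for Adverse Events (CTCAE), version 5.0". Seven events are to be recorded at each data collection interval: "dysuria, hematuria, incontinence, urinary retention, diarrhea, rectal hemorrhage, fatigue".
- Endpoints: one secondary endpoint is "Physician-reported GU/GI toxicity at 1, 3, 6, 9, 12, 18, 24-months (CTCAE"), and a separate one is "Patient-reported GU/GI toxicity at 1, 3, 6, 9, 12, 18, 24-months (IPSS, EPIC, SHIM").
- Pretreatment evaluation calls the questionnaire "the global quality of life measure EPIC-26", and Patient monitoring describes it in the same terms.

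The Analysis plan also sets out a chi-square comparison of the distribution of grades 0 to 5 for a selection of adverse events, and relative risks with 95% confidence intervals for grade 2 or 3 events. A later sentence says that patient-reported and physician-reported effects will be compared at 6 months, 1 year and 2 years, and qualifies those effects as treatment-related.

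**The concern.** There are two separate problems.

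The first is which instrument measures adverse events. A self-completed questionnaire is called objective and is put first for AEs, while other sections, and other sentences of the same section, rely on CTCAE grades. The Conclusion looks ahead to a claim that the 2-fraction regimen is non-inferior in safety as well as efficacy. If the two instruments point in different directions, the plan as worded would support leading with either, and that choice could be made after the results are known.

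The second is attribution. The document describes no blinding, and a man who receives 2 fractions rather than 5 will know it, as will his clinicians. If the dated comparison counts only events judged to be caused by treatment, that judgement could differ by arm. A comparison of all recorded events, whatever their supposed cause, does not depend on it.

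**Working it through.** The plan gives no figure on this point, and the sample size calculation does not bear on it. The check is a comparison of sections.

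**1. Is EPIC-26 objective?** The Endpoints section places EPIC under patient-reported toxicity, with IPSS and SHIM. Pretreatment evaluation and Patient monitoring both call it a quality-of-life measure. No section describes it as clinician-assessed or as an objective test. On the document's own terms the adverb is wrong.

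**2. Can EPIC-26 supply the planned AE comparisons?** Those comparisons need a grade from 0 to 5 for each event. Within the document, EPIC-26 yields domain points, interpreted through MIDs of 5, 6, 8 and 11. No rule converts points to grades. Its output is also by domain, whereas the list in Patient monitoring is by event. The chi-square and relative-risk analyses can therefore only come from CTCAE.

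**3. Which instrument is named for AEs?** Patient monitoring and the physician-reported endpoint say CTCAE v5.0. The sentence in the Analysis plan says EPIC-26, primarily. Both are current text and they cannot both stand as written.

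**4. Where does an attribution limit appear?**

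- Graded chi-square and relative-risk sentences: none.
- The two toxicity endpoints in the Endpoints section: none.
- The seven events recorded at each interval: none attached to the list.
- AE definition in Patient monitoring: "An AE is defined as any untoward medical occurrence associated with the use of a medical intervention". *Associated* can be read as timing or as cause, so this leaves the matter open.
- The sentence on 6 months, 1 year and 2 years: yes, the effects are qualified as treatment-related.
- Data and safety monitoring committee: it judges relatedness for grade 3 to 5 toxicity, as part of oversight. This is not stated to be a filter on the analysis.

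One comparison is thus worded as attributed and the graded tables are not. The document does not say how the two fit together.

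**The case against.** The strongest reply is that nothing is lost. CTCAE is still collected as a secondary endpoint, the graded comparisons are still planned, both patient-reported and physician-reported effects are to be compared, and the monitoring committee reviews any grade 3, 4 or 5 toxicity. On this view the sentence is a slip of wording that means only that EPIC-26 is the main questionnaire. Most of this stands, and it is why the point is minor. It does not remove the conflict, because the sentence speaks of AEs and of the primary measure, not of questionnaires.

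A reader might infer more than the document supports:

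- **That the EPIC-26 sentence itself limits the comparison to attributed effects.** It does not. A domain score carries no judgement of cause, so an EPIC-26 comparison is free of attribution. The limit comes from a different sentence.
- **That the graded tables are filtered by attribution.** They are not; those sentences contain no such condition. Nor does any section describe treating clinicians making a causality call before the arms are compared.
- **That severe events would be hidden behind a mean score.** The plan does not say that means will be compared; the MIDs would equally allow a count of men who change by more than the threshold. Severe events are in any case captured by CTCAE and reviewed by the committee.

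It is also fair to say that an article condenses a fuller protocol, so missing detail on AE analysis is no fault. The point here concerns sentences that are present and disagree.

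**Conclusion.** The point holds as a minor one, in two parts. First, the Analysis plan mislabels a patient-reported instrument as objective and names it as the primary measure of treatment-related AEs, against the document's own assignment of AE grading to CTCAE v5.0. Second, it words the comparison at 6 months, 1 year and 2 years as one of treatment-related effects, while the graded tables and the recorded event list have no such limit.

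No numerical size can be given. The document contains no toxicity rates or attribution rates for this comparison from which a bias could be calculated. The toxicity endpoints are secondary and unpowered, and the primary endpoint is unaffected.

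The attribution part rests on one inference: that patients and clinicians know the assigned arm. The document does not use the term open-label, but it describes no blinding and the number of visits differs between arms.

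**What to change.** Revise the wording of the Analysis plan:

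1. Delete *objectively*.
2. Name CTCAE v5.0 as the measure of graded, physician-reported AEs, and EPIC-26 with its stated MIDs as the main patient-reported measure. Present the two alongside each other, so that neither replaces the other.
3. State that CTCAE events are compared between arms at all planned time points regardless of attribution, with treatment-related events given as a supportive table.

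The AE definition in Patient monitoring should be read against item 3, so that its link to the interventions is not taken as a condition for recording or counting an event.

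The cost is a change of text; the instruments and visits are already in the schedule of assessments. The downside is that all-cause rates will be slightly higher and will include some unrelated urinary and bowel events in both arms.

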### Data and safety monitoring committee

A predefined international independent data and safety monitoring committee will evaluate the acute toxicity profiles of the first three patients treated with 2-fraction SABR for approval to proceed, and again after treatment of the first 20 patients. The committee will review the chart and treatment plant of any patient who experienced a grade 3, 4, or 5 toxicity, and can, at it’s discretion, recommend early closure of the trial, dose adjustments, or protocol amendment. The committee will meet annually after study initiation to review toxicity outcomes. If any grade 3–5 toxicity is reported, the committee will review the case to determine if such toxicity was related to treatment. The committee can, at its discretion, recommend cessation of the trial or exclusion of certain treatment sites and/or delivery techniques that are deemed as high-risk for complications.

### Confidentiality of subject records

All personal healthy information of study participants will be kept de-identified and confidential. Identification of subjects will be through a numbering system coded uniquely for this trial. The subject identifier list matching participants with their code will be kept confidential by the principal investigator and lead trial coordinator. No public reports will contain any identifying information of any individual patient.

